#### Exclusion criteria

Participants will be excluded for safety reasons, if they are pregnant, have any known allergies to chemicals, latex, or materials commonly found in a dentist’s office, or have an *in-situ* tracheostomy. Additional exclusion criteria are applied to ensure that the data are strictly measuring dysphagia in stroke patients only. These criteria are: no history of major surgery to the head, neck or mouth (other than routine tonsillectomy or previous tracheostomy); no known history of progressive neurological disorder (for example, Parkinson’s disease, multiple sclerosis); and no current or concurrent use of oral motor exercises targeted at improving swallowing.

Note that the participant’s diet is neither an inclusion nor an exclusion criterion; participants may be on an oral or non-oral diet with or without texture modifications or recommended compensatory strategies and participate in the study provided they meet the inclusion criteria. Furthermore, the participant’s recommended diet texture can be changed at any time during the protocol, provided it is clinically warranted.

### Enrollment

Enrollment is currently in progress; the targeted completion date is 2014.

### Randomization

During the intake procedure, participants will be randomly assigned to either the TPPT or TPSAT treatment conditions using a sequence generated by http://www.randomizer.org. Randomization will be concealed using sequentially numbered, opaque sealed envelopes.

### Blinding

It is not possible to blind the participants or treating clinicians to the condition given the protocol differences in the two arms of the trial. All data analysis, including treatment outcome, will be blinded. For VFSS rating, individual swallow clips for the first three teaspoon-sized boluses of 22% w/v thin-liquid barium will be spliced from the recordings for each participant, and arranged in a randomized order in a master rating set. Two blinded speech-language pathologists will review and rate these recordings.

### Outcome measures

Three types of data will be collected in this study: tongue pressure parameters, measures of swallow response time from videofluoroscopy, and measures of swallowing safety from videofluoroscopy. We will collect baseline and post-treatment pressure parameters (amplitude, duration, and slope) for the rise and release phases of tongue pressure events during three reference tasks (non-effortful saliva swallows, effortful saliva swallows, and posterior maximum isometric pressure tasks).

Videofluoroscopic measures will be collected at baseline and after treatment using a standardized videofluoroscopy protocol recorded on a KayPentax Digital Swallow Workstation at 30 frames per second. Two parameters will be rated for each spliced 5 ml thin-liquid barium (22% w/v) swallow:

1. Swallow response time (that is, the time difference between the arrival of the bolus head at the mandibular ramus and the onset of hyolaryngeal excursion, calculated in milliseconds, based on the time code of the video recording.

2. A measure on the eight-point penetration-aspiration scale [7], which determines the severity of and response to entry of the bolus into the airway.

The primary outcome variable of interest will be a measure of the participant’s average swallow response time across a series of three thin-liquid swallows (each 5 ml in volume). The targeted outcome will be an average swallow response time value shorter than 350 ms.

### Sample-size calculation

Our prior study of treatment outcomes from the TPSAT suggests that one-third of patients in the control group are likely to exhibit improvement in the primary outcome variable (average swallow response time above vs. below 350 ms). A sample-size calculation was conducted using Study Size Software 2.0, modeling the expectation (in a 2 × 2 contingency table) that the TPPT treatment will yield a greater rate of improvement, that is, in at least 66% of participants, than the current 30% response rate seen in cases accrued in our lab in historical studies. Under these assumptions, a sample-size calculation shows that 29 participants per group are needed to demonstrate a significant difference in rate of improvement at a *P* value of 0.05 and a power of 0.8. Therefore, we have established a targeted sample size of 60 participants (30 participants per protocol).

### Data processing and analysis

The proposed analysis of differences in pressure measures will be a 2 (group) × 3 (task) × 2 (measurement point) repeated measures mixed-model analysis of variance. We will perform this analysis using SPSS’s mixed modeling procedure, which will allow us to model the covariance structure of the data accurately.

From the VFSS measures, the primary measure of interest will be a binary reduction of the participant’s mean swallow response time measure (less than or more than 350 ms). We will also record whether or not the participant’s worst penetration-aspiration scale score across the series of three teaspoon-sized boluses of thin-liquid barium is less than or more than 3, representing material remaining above and inside or below the supraglottic space, respectively, as the measure of swallowing safety. Two-by-two tables with chi-square tests will be used to test for differences in the proportion of participants in each treatment group with impaired versus normal swallow response time at the post-treatment VFSS, and also the proportion in each group who display impaired swallowing safety. Odds ratios for reduction in swallow response time and improved swallowing safety will be computed.

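### The tongue-pressure model leaves baseline as a free response level, so its group contrast is a raw change-score difference: valid, but less precise than a baseline-adjusted contrast from the same data

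*Protocol article*

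**What the plan says.** Under Outcome measures, the Protocol article states: "We will collect baseline and post-treatment pressure parameters (amplitude, duration, and slope) for the rise and release phases of tongue pressure events". These are recorded on "three reference tasks (non-effortful saliva swallows, effortful saliva swallows, and posterior maximum isometric pressure tasks").

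Under Data processing and analysis, the planned comparison of these measures is a "2 (group) × 3 (task) × 2 (measurement point) repeated measures mixed-model analysis of variance", fitted with the SPSS mixed procedure, "which will allow us to model the covariance structure of the data accurately".

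Read together, the two sections make baseline one of the two levels of the response factor. Neither mentions a baseline covariate or a common baseline mean for the two arms, and the article does not name the model term that serves as the treatment comparison.

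The sample-size section says "we have established a targeted sample size of 60 participants (30 participants per protocol"). That figure was derived for the binary swallow-response-time outcome. No standard deviation, correlation or power is given for pressure.

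**The concern.** Baseline pressure is to be collected before treatment, and randomisation makes its expected value the same in both arms. A model that estimates a separate baseline mean for each arm ignores that knowledge. Its group × measurement-point contrast subtracts the whole observed baseline difference, although only a fraction ρ of that difference is expected to carry through to the post-treatment value. Two things follow when ρ is below 1: the confidence interval is wider than it needs to be, and a chance baseline imbalance is over-corrected, moving the estimate in the opposite direction.

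The pressure parameters are the trial's direct evidence on whether the timing-focused training alters how pressure is generated and released. With about 30 participants per arm and a sample size set for another outcome, avoidable loss of precision on them matters.

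**Working it through.** **1. The plan's own figure.** The article's sample-size section arrives at 29 per group (significance level 0.05, power 80%), taking 66% under TPPT against 30% under control. The two-proportion formula is n = [1.960·√(2·p̄(1−p̄)) + 0.842·√(p₁(1−p₁)+p₂(1−p₂))]² / (p₁−p₂)². With p₁ = 0.30, p₂ = 0.66 and p̄ = 0.48, n = (1.960·√0.4992 + 0.842·√0.4344)² / 0.1296 = 29.03. The figure is reproduced (power at 29 per group is 0.7996). It concerns the binary primary outcome only, so there is no stated figure for pressure to check.

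**2. What the planned contrast estimates.** The factorial model has a free mean for each group × task × measurement-point cell. With complete data, every participant contributes the same six measurements, so the generalised least-squares estimates of the cell means are the raw cell means under any covariance matrix. The group × measurement-point contrast is therefore

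(post − baseline) in TPPT minus (post − baseline) in TPSAT.

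On one simulated dataset of 60 participants, a random-intercept mixed model, a generalised least-squares fit with an arbitrary 6 × 6 covariance and the plain difference in mean change all gave −0.05087. Modelling the covariance does not recover the lost precision.

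**3. Single task.** Assume equal variance σ² before and after treatment, correlation ρ, and n = 30 per arm.

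- Planned: Var = (2σ²/n)·2(1−ρ)
- Baseline-adjusted: Var = (2σ²/n)·(1−ρ²)
- Ratio, adjusted to planned: (1−ρ²)/[2(1−ρ)] = (1+ρ)/2

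The difference detectable with 80% power (two-sided 0.05) is (1.960 + 0.842)·SE. ρ is not in the article, so a range is assumed.

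| ρ (assumed) | Variance ratio | Detectable difference, planned (SD) | Detectable difference, adjusted (SD) |
|---|---|---|---|
| 0.3 | 0.65 | 0.86 | 0.69 |
| 0.5 | 0.75 | 0.72 | 0.63 |
| 0.7 | 0.85 | 0.56 | 0.52 |
| 0.9 | 0.95 | 0.32 | 0.31 |

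Estimating the baseline slope costs a little at this size, by a factor of about 1 + 1/56 = 1.018. Simulated ratios at 30 per arm were 0.66–0.68, 0.75–0.78 and 0.85–0.87 for ρ = 0.3, 0.5 and 0.7.

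**4. Chance imbalance.** One standard error of the baseline difference is √(2/30) = 0.26 SD. The change contrast is shifted by (1−ρ) times that, which is 0.13 SD at ρ = 0.5.

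**5. Effect averaged over the three tasks.** What counts here is the correlation R between the task-averaged baseline and the task-averaged post-treatment value. If all six measurements share one correlation ρ, then R = ρ / [(1+2ρ)/3] = 3ρ/(1+2ρ), and the ratio is (1+R)/2:

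- ρ = 0.3: R = 0.9/1.6 = 0.56, ratio 0.78
- ρ = 0.5: R = 1.5/2.0 = 0.75, ratio 0.875
- ρ = 0.7: R = 2.1/2.4 = 0.875, ratio 0.94 (about 0.95 with the slope cost)
- ρ = 0.9: R = 2.7/2.8 = 0.96, ratio 0.98, which the slope cost removes (0.98 × 1.018 = 1.00)

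**6. A single pooled baseline slope.** Suppose each task's own baseline enters one mixed model with a common slope. That slope blends the within-person and between-person relations, while the overall group effect needs the between-person one. Under a shared correlation the within-person slope is zero, so the pooled slope is too shallow. Simulated variance of the overall effect relative to the planned contrast was about 0.90–0.95 at ρ = 0.3, 1.12–1.22 at ρ = 0.5 and at least 1.25 at ρ = 0.7. Where between-task correlation (0.5 assumed) and pre/post correlation multiply, the same model does gain (about 0.66, 0.76 and 0.83). Its performance therefore depends on a structure nobody knows in advance.

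**The case against.** The best defence is that this is a preference about efficiency. The planned analysis is a standard one; in simulation its type I error was 0.045–0.053, the same range as for the adjusted analysis. The outcome is not primary, the trial calls itself exploratory, and no power is claimed for pressure. The size of any gain rests entirely on assumed correlations, and it almost disappears when ρ is high.

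All of that stands, and it limits how much weight the point can bear. It does not remove the point. The article fixes the factors, their levels and the software procedure, so this is not a detail left to a document not shown, and the more precise analysis needs no additional data.

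The article's reliance on covariance modelling is a weaker defence: step 2 shows that no covariance structure changes the estimate with complete data while the baseline means are free.

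A reader might also infer that the group main effect will be taken as the treatment effect, which would average pre- and post-treatment values and show only half of any effect. The article never names that term as its comparison, so this criticism is not supported.

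**Conclusion.** The point holds as one of efficiency on a non-primary outcome. The planned group × measurement-point contrast is unbiased over randomisation and valid, but less precise than a baseline-adjusted contrast unless ρ is close to 1. Under equal variances and complete data, the variance reduction for a single task is about 35%, 25%, 15% and 5% at ρ = 0.3, 0.5, 0.7 and 0.9, slightly less at 30 per arm. For the three-task average it may be only about 22%, 13% and 5% at ρ = 0.3, 0.5 and 0.7, and negligible near 0.9.

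Two stronger readings should be resisted. A reader might infer that the pressure results would be biased or the test invalid; randomisation rules that out, and the effect of imbalance is conditional on the chance draw. A reader might also turn the single-task ratios into a fixed number of participants saved; the article gives no correlation, and the ratio depends on how the tasks correlate. The primary chi-square test and the 30 per arm are untouched.

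**What to change.** In Data processing and analysis, replace the pressure-analysis sentence with one of the following.

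- **Constrained baseline.** Keep both time points in the same SPSS mixed model, but constrain the group means to be equal at baseline within each task: fixed effects for task, measurement point and their interaction, plus a group effect at the post-treatment point for each task, with no group term at baseline. Use an unstructured covariance over the six measurements (6·7/2 = 21 parameters) or a similarly flexible one.
- **ANCOVA.** For each task, regress the post-treatment value on group and that task's baseline. For the overall effect, regress the task-averaged post-treatment value on group and the task-averaged baseline.

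Do not use one pooled slope on task-specific baseline in a joint model, because it can lose precision for the overall effect.

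State that the treatment effect is the adjusted post-treatment group difference, reported by task and overall for each pressure parameter. The cost is a few lines of analysis wording; participants, measurements and software stay the same. The change should be made before any analysis by arm.

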### Study population

The participants enrolled in this study will have a primary diagnosis of stroke, as well as dysphagia presenting with prolonged swallow response time for thin liquids. Impaired swallow response time will be operationally defined as the presence of thin liquid in the pharynx (that is, below the shadow of the ramus of the mandible) for >350 ms prior to the onset of hyolaryngeal excursion. This threshold value falls halfway between the reported 95% confidence intervals for non-aspirating and aspirating stroke patients in a recent study [8]. We will measure this parameter on 5 ml swallows of thin-liquid barium using a cued swallow instruction. Participants must be patients (inpatient or outpatient) in one of the two participating rehabilitation settings to be enrolled in the study. Additional inclusion and exclusion criteria are detailed.

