#### Inclusion criteria

To be included in the study, each participant must be able to understand English, be able to follow directions, and be able to tolerate oral trials under the supervision of a therapist. This is likely to exclude individuals with brainstem strokes, for whom swallowing is often profoundly impaired and oral trials are often unsafe. Additionally, to control for spontaneous recovery, enrollment into the study must occur at least four weeks after dysphagia onset and not more than 20 weeks following dysphagia onset. Within this enrollment window, a VFSS must be completed and recorded. The VFSS recording will then be scored by a speech-language pathologist to determine whether poor bolus control is present, as indicated by swallow response times >350 ms on teaspoon-sized volumes of thin-liquid barium. This will confirm eligibility to participate.

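### The primary responder comparison is an unadjusted chi-square test, although the baseline swallow response time that could sharpen it is already collected

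*Protocol article*

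**What the plan says.** Under Outcome measures, swallow response time is calculated in milliseconds from recordings at 30 frames per second. The primary outcome variable is the participant's average over three 5 ml thin-liquid swallows, with an average under 350 ms as the target. The same section shows that a baseline value will exist: "Videofluoroscopic measures will be collected at baseline and after treatment using a standardized videofluoroscopy protocol".

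Data processing and analysis then states that "the primary measure of interest will be a binary reduction" of that mean at 350 ms and names the test: "Two-by-two tables with chi-square tests will be used to test for differences in the proportion of participants in each treatment group", the proportions being those with "impaired versus normal swallow response time at the post-treatment VFSS". Odds ratios will also be computed. The section states no baseline-adjusted analysis of swallow response time; its mixed model is for the tongue pressure measures only.

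The cut is also the entry criterion. Inclusion criteria require poor bolus control, "as indicated by swallow response times >350 ms on teaspoon-sized volumes of thin-liquid barium". Study population gives the reason for the value: "This threshold value falls halfway between the reported 95% confidence intervals for non-aspirating and aspirating stroke patients". Sample-size calculation works from a 2 × 2 table with 30% versus 66% improving and arrives at 29 per group, rounded to 30.

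**The concern.** Everyone enters on the basis of response times above 350 ms, and success means finishing with a mean below 350 ms. Baseline status as a dichotomy is therefore nearly constant and tells the analysis almost nothing. The baseline value in milliseconds is different: a participant just above the threshold has much less ground to cover than one far above it. If so, baseline explains part of the variation in success, and a test that ignores it carries that variation as noise.

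What is at stake is power in a 60-patient trial whose margin is thin. The chi-square reaches 80% power at 30 per group only if the TPPT rate is about 65.5% or more against 30%. At 55% versus 30% its power is about 0.50. The analysis could use a measurement that the trial already takes.

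**Working it through.** **Inputs from the article.** Rates of 30% and 66%, significance level 0.05, power 0.80, 29 per group needed and 30 planned (Sample-size calculation); the 350 ms cut; 30 frames per second; three swallows. Sidedness is not stated; a two-sided test reproduces the figure.

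**Not in the article, so assumed.** The SD of the outcome, the shape of its distribution, and the correlation r between baseline and post-treatment response time. The range used is r = 0.3 to 0.7.

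**1. The plan's own figure.** With a mean rate of (0.30 + 0.66)/2 = 0.48:

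- n = [1.96 × √(2 × 0.48 × 0.52) + 0.842 × √(0.30 × 0.70 + 0.66 × 0.34)]² / 0.36² = (1.385 + 0.555)² / 0.1296 ≈ 29.0. This rounds up to 30; the arcsine formula gives 28.9.
- Power at 29 per group is 0.800, so the stated 29 is reproduced.
- Power at 30 per group: SE under the null = √(2 × 0.48 × 0.52/30) = 0.129; SE under the alternative = √(0.4344/30) = 0.120; Φ[(0.36 − 1.96 × 0.129)/0.120] ≈ 0.81.

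**2. Why baseline is likely to matter.** One frame is 1000/30 = 33.3 ms, so a three-swallow mean moves in steps of 33.3/3 = 11.1 ms. A hypothetical participant with a baseline mean of 355.6 ms (32 steps) becomes a success at 344.4 ms (31 steps), a change of one frame on one swallow. A participant several hundred milliseconds higher needs a change many times larger. The article gives no baseline distribution, so how many participants lie near the cut is unknown.

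**3. Same binary endpoint, adjusted for baseline.** Suppose post-treatment response time is normal with a common shift between arms and correlates r with baseline. The shift that gives 30% and 66% below the cut is d = z(0.66) − z(0.30) = 0.412 + 0.524 ≈ 0.94 SD. Simulated power at 30 per group:

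| Analysis of the proportion below 350 ms | r = 0.3 | r = 0.5 | r = 0.7 |
|---|---|---|---|
| Chi-square, unadjusted | 0.81 | 0.81 | 0.81 |
| Logistic model with continuous baseline | 0.85 | 0.88 | 0.94 |

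The Wald form of the logistic test is slightly less powerful than the likelihood-ratio form but holds its level better, so the plan should name the one used.

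**4. When baseline does not predict success.** In a responder model, 30% and 66% normalise regardless of baseline and the rest stay near where they started. Power is 0.81 for the chi-square and 0.81 for the adjusted logistic model, so the adjustment costs essentially nothing.

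**5. Analysis in milliseconds.**

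- *Common normal shift.* Unadjusted power is Φ(0.937 × √(30/2) − 1.96) = Φ(1.67) = 0.95. Dividing the shift by √(1 − r²) gives 0.97, 0.99 and 0.999 for r = 0.3, 0.5 and 0.7. Simulated ANCOVA with baseline truncated at entry gives 0.955, 0.966 and 0.990.
- *Strongly skewed (log-normal) times, untransformed.* ANCOVA 0.86 to 0.94, chi-square 0.81 to 0.84.
- *Responder model* (illustrative baseline log-normal with median 620 ms, truncated at 350 ms, log-SD 0.4 to 0.8). Chi-square about 0.81; ANCOVA 0.58 to 0.70. Another version of the model gives ANCOVA 0.44 to 0.66 and a rank-based analysis 0.69 to 0.71. The order reverses.

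**The case against.** The binary endpoint is deliberate and coherent. One construct, 350 ms, defines impairment, eligibility, the target, the sample size and the test, and its value has a stated rationale. The plan has about the power it claims. The trial is labelled small and exploratory, and supportive analyses may be described elsewhere. Most of this stands, and the recommendation therefore leaves the endpoint in place.

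Three stronger readings are tempting.

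- *The cut throws away much of the information, so a mean difference in milliseconds should replace the responder proportion.* Under a common normal shift, 18 per group would do the work of 30, a loss of 1 − 18/30 = 40%. The documents give no SD, correlation or distribution to support that model. The Background says that about 30% of patients completing TPSAT improve functionally, which makes a responder pattern plausible, and under that pattern the advantage reverses. Replacement would also change the question from reaching a functional target to an average change, for which the article states no important difference and no sample-size basis.
- *Chance imbalance in baseline severity biases the comparison.* Allocation is random and concealed in sealed envelopes, so the chi-square remains valid. Imbalance costs precision only.
- *A large fall that stops just above 350 ms is wrongly counted as failure.* That follows from a target defined as functional response time. It is a consequence of the chosen endpoint, not a mistake.

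The objection does not reach the missing adjustment. The article names the primary test explicitly, and that test makes no use of baseline. Adjusting it keeps the endpoint, cut and target rates.

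**Conclusion.** The point holds as a modest efficiency weakness in the primary test. At 30 per group, baseline adjustment of the same binary endpoint would raise power from about 0.81 to between 0.85 and 0.94 if response times shift roughly normally and baseline correlates 0.3 to 0.7 with outcome. It would leave power essentially unchanged if baseline does not predict success. Both the shift model and the correlations are assumptions.

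The larger gain from a millisecond analysis (power of about 0.96 to 0.99) holds only under a common normal shift. Under a responder pattern that analysis can be weaker than the planned chi-square. It merits a supportive role, and the documents do not justify making it primary.

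**What to change.** Before unblinding, amend the analysis as follows.

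1. Keep the proportion with mean swallow response time below 350 ms at the post-treatment VFSS as the primary endpoint. Compare arms with a logistic model containing treatment and continuous baseline mean swallow response time, and name the test (Wald or likelihood-ratio). The dichotomised baseline is nearly constant by design and should not be the covariate.
2. Report the standardised risk difference with its confidence interval beside the odds ratio. The adjusted odds ratio is a different quantity from the one read off the 2 × 2 table, whereas the risk difference stays on the scale of the sample-size assumptions.
3. Keep the chi-square test as a sensitivity analysis.
4. Pre-specify, as a key supportive analysis, an ANCOVA of post-treatment mean swallow response time in milliseconds on arm and baseline, with a rank-based version if residuals are skewed. State that its efficiency depends on how treatment acts.

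No new data, visits or patients are needed, and the sample size keeps its basis. The cost is slightly more analysis work and a headline estimate that is adjusted for a covariate.

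### The odds ratio for improved swallowing safety appears to rest on post-treatment status alone, so participants already safe at baseline would count as improved

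*Protocol article*

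**What the plan says.** Under Data processing and analysis, the article defines swallowing safety as a status: whether the participant's "worst penetration-aspiration scale score across the series of three teaspoon-sized boluses of thin-liquid barium is less than or more than 3". Chi-square tests on 2×2 tables are to compare the arms on "swallow response time at the post-treatment VFSS, and also the proportion in each group who display impaired swallowing safety". The next sentence reads "Odds ratios for reduction in swallow response time and improved swallowing safety will be computed". The section gives no definition of improvement, no baseline term and no restriction to participants impaired at baseline.

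Entry is set on a different measure. Study population requires "dysphagia presenting with prolonged swallow response time for thin liquids", and Inclusion criteria confirms eligibility by poor bolus control "as indicated by swallow response times >350 ms on teaspoon-sized volumes of thin-liquid barium". No criterion mentions the penetration-aspiration scale. Exclusion criteria adds that the participant's "diet is neither an inclusion nor an exclusion criterion", so diet does not stand in for a safety requirement. Outcome measures states that the videofluoroscopic measures, which include the penetration-aspiration score, are taken both at baseline and after treatment.

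**The concern.** For swallow response time, reading post-treatment status as improvement largely works. Everyone enters above 350 ms, so a value below 350 ms afterwards is a change for the better. The same wording is then applied to safety, where no entry condition supports it.

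An unknown share of participants will already be safe at baseline. If they stay safe, they fall in the favourable cell of the safety table although nothing has improved. A participant who goes from safe to impaired shares a cell with one who was impaired throughout. An odds ratio from that table describes the odds of being safe after treatment, not the odds of improving. It is pulled towards 1 by participants with no room to improve. With 30 per arm, it also carries any chance difference in baseline safety between the arms.

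This matters because the stated ultimate goal (Study objectives) is to restore functional swallowing in people who cannot swallow thin liquids safely. Readers will take an odds ratio for improved safety as evidence on that goal.

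**Working it through.** **Inputs from the article (Sample-size calculation).** 30 per arm; alpha 0.05 (two-sided assumed); response rates of 30% v 66%. These rates belong to the response-time outcome and are borrowed here, because the article gives no rates for safety.

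**Assumptions.** The share safe at baseline, s, is not given and is varied from 0.2 to 0.8. Participants safe at baseline all stay safe. Among those impaired at baseline, 30% (TPSAT) and 66% (TPPT) become safe.

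**The plan's own figure.** The stated 29 per group concerns the primary outcome only. The pooled-variance formula for 30% v 66%, two-sided, without continuity correction, gives 30 per group, and power at 29 is 0.80. The figure is reproduced to within one participant. The present point does not depend on it.

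**Dilution.** The probability of being safe after treatment is p = s + (1 − s)·c, with c = 0.30 or 0.66. The odds ratio is [p_T/(1 − p_T)] / [p_C/(1 − p_C)].

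- Among those impaired at baseline: (0.66/0.34)/(0.30/0.70) = 4.53.
- All participants, s = 0.4: p_C = 0.4 + 0.6 × 0.30 = 0.58 and p_T = 0.4 + 0.6 × 0.66 = 0.796. The odds ratio is (0.796/0.204)/(0.58/0.42) = 2.83.

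**Power** (normal approximation), with d = p_T − p_C and p̄ the mean of the two rates: Φ{[d − 1.96·√(2p̄(1 − p̄)/n)] / √[(p_C(1 − p_C) + p_T(1 − p_T))/n]}.

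- All participants, s = 0.4, n = 30: Φ[(0.216 − 0.2345)/0.1163] = 0.44.
- Impaired at baseline only, n = 18: Φ[(0.36 − 0.3264)/0.1553] = 0.59.

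| Safe at baseline (s) | Safe after, TPSAT v TPPT | Odds ratio, all | Already safe, as share of TPSAT safe cell (s/p_C) | Power, all (30 per arm) | Power, impaired at baseline only (n per arm) |
|---|---|---|---|---|---|
| 0.2 | 0.440 v 0.728 | 3.41 | 45% | 0.62 | 0.72 (24) |
| 0.4 | 0.580 v 0.796 | 2.83 | 69% | 0.44 | 0.59 (18) |
| 0.6 | 0.720 v 0.864 | 2.47 | 83% | 0.28 | 0.42 (12) |
| 0.8 | 0.860 v 0.932 | 2.23 | 93% | 0.15 | 0.22 (6) |

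The approximation is rough in the last row.

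**Chance imbalance.** Suppose each participant has a one-half chance of being safe at baseline. With two independent binomial counts of 30, the arms differ by 6 or more in 15.5% of randomisations, about 16%, counting both directions. If 18 v 12 were safe at baseline and nobody changed, the odds ratio would be (18/12)/(12/18) = 2.25. The standard error of its logarithm is √(1/18 + 1/12 + 1/12 + 1/18) = 0.527, so the 95% confidence interval is 0.80 to 6.3. The uncorrected chi-square is 60 × (18 × 18 − 12 × 12)²/30⁴ = 2.4, p = 0.12.

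**The case against.** Four objections carry weight.

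*The link is inferred.* The article does not say that the odds ratio comes from the post-treatment table. The time point is attached to response time and reaches safety only through the conjunction, and the odds-ratio sentence uses words of change. A fuller analysis plan could define improvement from the two scores. This stands as a limit on certainty, so it would be too strong to say that the article rules out use of the baseline score. But the section describes no other safety table and no definition of change, so the natural reading is a status table with an improvement label.

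*The comparison is valid.* A reader might infer that the treatment comparison is biased. It is not: randomisation makes the comparison of post-treatment status unbiased, and the test's error rate already allows for chance imbalance. Baseline adjustment is a gain in precision and interpretation, not the repair of an invalid test. This stands in full.

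*The imbalance example can be over-read.* With half safe at baseline, the arms differ by 3 or more of 30 in 52% of randomisations. That frequency does not belong to the 18 v 12 example, which needs a difference of 6 (about 16%). Even then the planned test would not declare an effect.

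*The illustration is borrowed and the endpoint is secondary.* The 30% and 66% come from another outcome, and assuming that nobody deteriorates sets aside the very deterioration the table hides. The sizes are therefore indicative only. The primary outcome and the sample size are not touched.

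**Conclusion.** The point holds as a fault of labelling and efficiency in a secondary endpoint. On the natural reading, the quantity called an odds ratio for improvement is an odds ratio for being safe after treatment, and it includes participants who could not improve.

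Under the stated assumptions the distortion is material. With 20% to 80% safe at baseline, an odds ratio of 4.5 for true improvement is reported as 3.4 down to 2.2. Restricting to those impaired at baseline gives higher power at every share examined, despite smaller numbers. All of this depends on the assumed baseline-safe share, the borrowed rates and no deterioration; with nobody safe at baseline the problem disappears. The documents do not support a claim of systematic bias or any effect on the primary analysis.

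**What to change.** Analyse post-treatment safety with a logistic model containing treatment arm and baseline safety (penetration-aspiration) status, and label its odds ratio as safe status after treatment. Compute any odds ratio for improvement only among participants impaired at baseline, defined as impaired before and safe after. Report new impairment among those safe at baseline separately, and show baseline safety by arm.

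The cost is a change of analysis wording. The baseline score is already rated, so no new data, visits or participants are needed. The downside is that the improvement odds ratio rests on fewer participants. Also, if no baseline-safe participant becomes impaired, ordinary maximum likelihood cannot estimate the baseline term, so the plan should name a fallback such as penalised likelihood.
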